### Implementation of the Trial and Patient Information

The new patients with pulmonary TB will be recruited to the VOT or DOT group by the TB nurse, depending on the jurisdiction of residence of the observer.

The relevant information regarding the study will be provided to potential patients prior to the start of the trial, including highlighting who can observe them taking their medication (ie, their observer and the auditor) along with the possible assigned interventions (VOT or DOT). The observer’s intervention group will not be revealed before they consent to participate. If the patients consent to participate, they will be assigned to the same intervention group as the observer of their PCU. They will be free to refuse the intervention at any point, and those who refuse or withdraw from the study will continue with traditional DOT without study data collection.

### Blinding

The observers will disclose their assigned intervention to the auditor, TB nurses, and researchers. Next, the researchers will train the VOT observers to familiarize them with the TH VOT system [9]; the DOT observers will be requested to perform traditional DOT as routine care. Thus, none of the researchers or staff involved in the study will be blinded to the assigned interventions.

### Statistical Analysis

Background information of patients and observers will be summarized using descriptive statistics.

An intention-to-treat analysis will be performed according to the randomized allocation. Thus, participants will be classified according to the intervention group to which they are assigned, regardless of their actual intervention.

We will compare the percentages of compliance between the two interventions at 60 days after treatment initiation. The 60-day compliance of the individuals will be defined as the percentage calculated using the following formula: (mean cumulative compliance days×100)/60. Our study is a cluster randomized controlled trial; thus, the cumulative number of compliant days of patients and observers will be nested in clusters. We will analyze their 60-day compliance considering that the same observer may monitor more than one patient. The intervention effect will be based on a linear mixed-effects model [22]. According to our study design, the intervention will be a fixed effect, whereas the cluster level will be a random effect.

The number of compliant days of patients and their observers will be visualized using solid green dots indicating the daily compliance of the individual subjects (Y-axis) and the elapsed number of days since starting the medication (X-axis). To investigate the dynamics of compliant days of the patients and observers over time, the mean cumulative number of complaint days within each group will also be plotted. The estimation of mean cumulative compliant days will range between 0 and 60, with 60 indicating that all participants in the group completed their daily sessions for 60 days. The function will be plotted using the mean cumulative number of compliant days (Y-axis) and the elapsed number of days since the start of medication administration (X-axis). Ideally, a steady increase in linear trend with a 45° slope indicates 100% compliance at any point from 0 to 60 days. Flattening of the slope represents a decline in the compliance percentage over time within the group.

Only descriptive statistical methods will be used on the aforementioned clinical outcomes and noncompliance activities of the observers because we may not have sufficient statistical power to detect small differences.

### Ethics Approval

The Human Research Ethics Committee, Faculty of Medicine, Prince of Songkla University approved the trial on February 19, 2021 (approval number 64-03618-9).

### Data Sharing

Data and programming R codes used in this trial are available in a GitHub repository [23].

## Results

This study is being supported by the Fogarty International Center and the US National Institute of Allergy and Infectious Diseases of the US National Institutes of Health under Award Number D43 TW009522 (June 14, 2021). The researchers and Deputy Province Chief Medical Officer of Songkhla Provincial Public Health Office came to an agreement on the implementation of the VOT on June 22, 2021. Recruitment started in January 2022 and will end in July 2022. The observation period is scheduled to end by September 2022.

## Discussion

### Summary

The DOT program is not sustainable in Thailand, especially during the COVID-19 pandemic period. The VOT program is a good alternative to remotely observe TB patients. The present trial will confirm whether compliance is better in observers assigned to VOT than in observers assigned to standard community-based DOT. The cluster randomized superiority trial design will minimize confounding variables and strengthen the evidence base for VOT.

### Potential Strengths

This study will assess the compliance effect on both patients and their observers in a cluster, which is more practical than using an individual effect. Compliance of both patients and observers under community-based DOT, which has rarely been studied, will be assessed in this cluster randomized superiority trial. Although treatment group blinding is not possible [24], both groups will be under the same level of monitoring by the auditor. Thus, the Hawthorne effect will be balanced.

Previous VOT versus DOT comparative studies [10,11] have been based on an overall assessment, including ordinary percentage of compliance. Our mean cumulative function analysis will determine periods with weak compliance. This can be used to reinforce observation compliance in the future.

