### Study Design

We will perform a cluster randomized controlled trial. An observer will be assigned a cluster of patients with pulmonary TB that live in the same jurisdiction, either using DOT or VOT. We aim to observe each patient for 60 days during the intensive phase of their TB treatment. Daily compliance will be audited by one auditor who will supervise all observers in the study area according to a standard assessment protocol [9]. The study flow is summarized in Figure 1.

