### Procedures for the Auditor to Review Each Video/Picture Session

#### Sessions in the VOT Group

“Day” will be used as the time unit for judging compliance, and local times (Greenwich Mean Time+7 hours) will be recorded. The morning will begin at 12 AM (midnight) and the evening will end at 11:59 PM. However, daily compliance will be judged as “achieved within the cut-off time” if the patients take their medication and submit their videos before 6 AM the following day. The auditor will assess daily video sessions for patients within 24 hours of the video upload. Assessment items include whether the VOT has been administered, if the patients followed the SOP, and whether they were observed as per the protocol or properly reminded by their observer. The auditor will interpret each session based on the SOP modified from the previous study [9].

The patient will be considered to have daily compliance if the video is sent within the stipulated time and if its quality meets the following criteria: (1) the patient’s face and the drug tablets/capsules are clearly visible in the video frame, (2) the pills are picked up from the drug plane and placed on the tongue, (3) the pills are swallowed with water from a (clear) glass, (4) the tongue is raised to show the sublingual area and stuck out to show the palate area, and (5) steps 2 to 4 are repeated until all pills are consumed.

The observers will be considered compliant if they adhere to the following quality standards: (1) correctly assess whether the patient performs the aforementioned steps, (2) note the number of pills consumed by the patient in the video correctly, and (3) follow up with patients via phone calls if they perform any procedure incorrectly. The TH VOT system can detect whether the observers have already made a phone call to their patients.

The daily session scored by the auditor will be recorded as 1 for daily compliance or 0 otherwise. The approval platform of the TH VOT system will automatically save all lists of the steps approved and the daily compliance score to the server database. If a patient does not record a video following the SOP, the auditor will make a phone call to remind the observer to correct the patient’s mistakes. If a patient does not send a video for 7 consecutive days, they will be considered to have discontinued the intervention.

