#### Sessions in the DOT Group

The auditor will score the daily compliance weekly based on the booklet photos sent by the TB patients and their observers. The patients will be considered to have daily compliance as reported (no audit). The auditor will make a phone call to the TB patients to confirm if they were observed as reported by their observer and to remind them to safely store the booklet and all zipped bags received from the TB clinic. If the patients report that they were not observed, the auditor will further investigate and record the observer’s actions such as making phone calls instead of in-person visits to check patients’ daily drug administration, missing patient appointments, or performing activities not included in the in-person DOT protocol.

A daily session reported by the observer will be scored as 1 for daily compliance as confirmed by the patients and 0 otherwise. If a patient misses a phone call twice or loses the booklet and/or the blank zipped bags, they will be discontinued from the intervention and their daily scores of the previous 7 days will be 0. All scored sessions will be recorded in the DOT record system of the server. The activities of observers not included in the in-person DOT will also be recorded.

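### The claim of equal auditor monitoring and a balanced Hawthorne effect is contradicted by the auditor procedures, and auditor prompting can raise VOT scores by an amount the protocol cannot size

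*Protocol article*

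**What the plan says.** The Discussion (Potential Strengths) accepts that blinding is impossible and offers this in mitigation: "both groups will be under the same level of monitoring by the auditor. Thus, the Hawthorne effect will be balanced". Study Design gives a similar impression: "Daily compliance will be audited by one auditor who will supervise all observers in the study area according to a standard assessment protocol".

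The arm-specific auditor procedures differ. For VOT: "The auditor will assess daily video sessions for patients within 24 hours of the video upload". When a video does not follow the SOP, "the auditor will make a phone call to remind the observer to correct the patient’s mistakes". For DOT: "The auditor will score the daily compliance weekly based on the booklet photos sent by the TB patients and their observers". On DOT patients the section adds: "The patients will be considered to have daily compliance as reported (no audit".

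The Primary Outcomes section builds both patient and observer compliance from the auditor's daily scores. The Blinding section states that nobody on the research team or staff is blinded. The Limitations section raises possible over-reporting in DOT. From that it concludes that lower compliance in DOT than in VOT would settle superiority.

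**The concern.** The balance claim is the protocol's stated safeguard against reactivity in an unblinded trial with a behavioural outcome. If monitoring differs by arm, that safeguard is missing.

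The difference is also more than a matter of being watched. In VOT the person who scores compliance prompts the observer when something goes wrong, so the measurement process can improve the quantity it measures.

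This bears on the planned conclusion in two ways. First, the Limitations argument works only if every measurement problem runs against VOT: DOT may be overreported, so a VOT advantage must be real. A mechanism that can lift VOT scores breaks that argument. Second, the abstract and the Conclusion tie a positive result to replacing DOT with VOT. Readers would need to know that the tested package included near-daily external audit and feedback.

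**Working it through.** The protocol gives no figure for monitoring intensity, so the check is mainly a comparison of sections.

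**Auditor procedures by arm** (VOT and DOT auditor sections, DOT for Patients, DOT for Observers)

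| | VOT | DOT |
|---|---|---|
| Review schedule | Each uploaded video, within 24 hours | Weekly, from booklet photos |
| Patient standard | Timely upload plus five quality criteria | Self-report accepted |
| Observer standard | Three criteria, including a follow-up call after an incorrect procedure | Reported session confirmed by the patient |
| Auditor contact | Call to the observer when the SOP is not followed | Weekend photo requests to patient and observer; calls to patients to confirm observation and remind them about booklet and bags |
| Action on a fault | Observer prompted to correct it | Auditor investigates and records; no corrective call to the observer described |

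**Review occasions per patient over 60 days**

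- DOT: 60 / 7 = 8.57, so about 8 to 9.
- VOT maximum (an upload every day): 60. Ratio 60 / 8.57 = 7.0.
- VOT at the 65% compliance used in the Sample Size section: 0.65 × 60 = 39. Ratio 39 / 8.57 = 4.55. Every compliant day has an upload, and non-compliant uploads are reviewed too, so 39 is a floor if 65% holds.

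Reviews are therefore roughly 4.5 to 7 times as frequent in VOT. This counts review occasions only. Each weekly DOT review covers seven daily entries, so every day is scored in both arms, and the DOT prompts and calls are not counted.

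**Where prompting can reach the score**

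1. *Observer score, same session.* Criterion 3 requires the observer to phone the patient after an incorrect procedure. The auditor's call asks the observer to correct the patient's mistakes, so it can trigger the very action that earns the point. The section does not say whether the observer is scored before or after that call.
2. *Patient score, later days.* Correcting technique after one failed video can make later videos pass.
3. *Patient score, same day.* This route is weak. Review may come up to 24 hours after upload, while the cut-off is 6 AM the next day, and no rescoring of a failed video is described. Chasing an unsent video is the observer's task (VOT for Observers), not the auditor's.

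**Size.** The protocol does not say how often the auditor will call, or how often a call changes a score. It also does not say whether the 65% was obtained with such calls in place. No effect on compliance can be computed from it.

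**The case against.** The strongest reply is that the auditor is active in both arms. Study Design has one auditor supervising all observers under a standard protocol. DOT patients are prompted every weekend and phoned, and unobserved sessions are investigated. Two missed calls, or a lost booklet or bags, lead to discontinuation with the previous seven days scored 0. These contacts, and the self-recording booklet added to the national guideline's procedure, could themselves raise DOT compliance. This stands, and it rules out the reading that the auditor intervenes in VOT alone. It does not make the monitoring equal: frequency, depth and corrective feedback to the observer all differ. The general sentence in Study Design cannot override arm-specific procedures that say DOT patient compliance is not audited.

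A second reply is that other features favour DOT: VOT patients must pass five video criteria, while DOT patients are believed. This also stands. A reader might infer that the trial is biased towards VOT overall, but for patient compliance the documents leave the net direction open.

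A third reply is that a planned difference of 64 points leaves ample room. That holds if such a difference appears. However, it sets a 65% VOT patient figure against one observed DOT appointment in 60 days. DOT patient compliance by self-report could be far higher, and the contrast correspondingly smaller.

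**Conclusion.** The statement under Potential Strengths is wrong on the protocol's own procedures. Review occasions are up to 60 per patient in VOT against about 8 to 9 in DOT, and corrective feedback to the observer is described for VOT only. Auditor prompting can therefore raise VOT scores, most directly observer criterion 3 and patient scores on later days. It follows that lower DOT compliance would not by itself make VOT definitely superior.

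This conclusion rests on reading the auditor sections as complete for each arm. If the auditor also phones DOT observers to correct them, the imbalance is smaller, but the difference in schedule and depth remains.

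Two further inferences are tempting and not supported. One is a figure in percentage points for the inflation: nothing in the protocol supplies it. The other is that a routine VOT programme would lack this supervision. The protocol does not describe future audit arrangements, and the Introduction gives auditable records as a reason for choosing asynchronous VOT.

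The point is a correctable misstatement about a safeguard against bias, with a scoring rule to tighten. It does not invalidate the design.

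**What to change.** 1. *Potential Strengths:* delete the claim that monitoring is equal and the Hawthorne effect balanced.
2. *Limitations:* state that auditor contact differs in schedule, depth and feedback. Withdraw the sentence that VOT would definitely be superior if DOT compliance is lower.
3. *Sessions in the VOT Group:* score the observer's session on its state before any auditor call. Time-stamp auditor calls in both arms.
4. *Statistical Analysis:* add a sensitivity analysis that scores as 0 any VOT observer session made compliant only after an auditor call. This is most useful for sessions scored before the rule in item 3 applies, where call times can be recovered.
5. *Conclusion:* describe the tested intervention as VOT with near-daily audit and feedback.

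The cost is a call log and wording changes. The TH VOT server already saves approved steps and daily scores, and can detect whether an observer has phoned. VOT observer compliance may come out slightly lower, partly because some observers would have phoned without a prompt.

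None of this alters when or whether the auditor calls. Putting VOT feedback on a weekly schedule to match DOT is not recommended: recruitment has begun, and the change would reach beyond statistics into how drug-taking mistakes are corrected.

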### Limitations

Compliance of the patients in the VOT group will be directly recorded in the video records, which are accurate. However, compliance in the DOT group is only based on the patient’s report, which is not verifiable. The comparison is limited by the quality of compliance ascertainment in the DOT intervention group. The compliance of the DOT group may be overreported. If the compliance on the DOT side is lower than that on the VOT side, VOT would definitely be superior to DOT. Otherwise, the comparison may not be fully conclusive.

The main limitation is that the TB patients will not be followed up until the end of the treatment. The trial period is limited to the first 2 months of TB treatment (the intensive phase) owing to budget limitations. Sputum conversion is an uncertain surrogate of successful treatment. However, numerous studies have shown that sputum conversion is well-correlated with successful treatment [25-29].

### Conclusion

The study should provide evidence to determine whether a new policy for using VOT instead of traditional DOT for TB patients who own smartphones could improve the accountability of TB treatment monitoring. If the VOT intervention is shown to be superior to the community-based DOT intervention, we will advocate for VOT to replace the existing DOT.

## Appendix

Multimedia Appendix 1 CONSORT-eHEALTH checklist V 1.6.1.

## Abbreviations

AFB: acid-fast bacilli
A-VOT: asynchronous video-observed therapy
DOT: directly observed therapy
EHR: electronic health record
HRZE: isoniazid, rifampicin, pyrazinamide, and ethambutol
ICC: intracluster correlation coefficient
NTIP: National Tuberculosis Information Program
PCU: primary care unit
SOP: standard operating procedure
S-VOT: synchronous video-observed therapy
TB: tuberculosis
TH VOT: Thai video-observed therapy
VOT: video-observed therapy
